## Discussion

For people diagnosed with schizophrenia who are unable to tolerate, or whose symptoms have a limited response to clozapine there is limited evidence for alternative treatments. There is therefore, an urgent need to evaluate evidence-based treatment options for this group of people. To our knowledge, our trial is the largest definitive trial of CBTp to date. It is the first multi-site, randomised, controlled trial of its size to investigate the clinical and cost effectiveness of CBTp in a strictly-defined, clozapine-resistant schizophrenia group. Recruitment to the trial has ended and we have recruited successfully to target. Indeed, we over-recruited to the trial by two participants, achieving a final total of 487 out of a target of 485.

Our trial has a number of unique features. A strength of the trial is that we collect the primary outcome data 12-months from the end of the treatment window. This provides an opportunity to determine the medium-range effects of CBTp and is unlike many other trials that have a primary outcome at end of treatment [58]. This is likely to be of particular importance given the findings from a meta-analysis of CBTp that the benefits of CBT may be delayed for up to a few months after treatment has ended [58].

Understanding and quantifying the risk of potential adverse effects of CBTp is important and early CBTp trials have been criticised for not giving this issue adequate consideration [59]. Klingberg et al. [60] have provided a useful template for assessing adverse effects as defined by the following criteria: (1) death by suicide, (2) suicide attempt, (3) suicidal crisis (explicit plan for serious suicidal activity without suicide attempt as defined by item 8, rating of 2 on the Calgary Depression Rating Scale for Schizophrenia; CDSS) and (4) severe symptomatic exacerbation (defined by the Clinical Global Impression Scale; CGI). We measure and report criteria 1–3 as part of National Research Ethics Committee requirements for recording and reporting serious adverse events. Additionally, we capture potential unwanted side effects from trial participation from scores on the CDSS and CGI. We will report scores of 6 or more on the GCI-Improvement Scale at 9 and 21 months’ follow-up. Furthermore, in order to capture the participants, own experiences and perspectives on trial participation we developed a bespoke measure of adverse effects from trial participation, which participants complete at the 21-month follow-up or are were offered at the point of withdrawal from the trial. Item generation was via a review of relevant literature on assessing adverse effects in psychotherapy trials [60, 61]. In relation to CBTp, we are also exploring the acceptability of CBTp through a qualitative evaluation of participants’ subjective experiences and perceptions of CBTp during the FOCUS trial. This aspect of the trial is led by service users.

It is unclear from the literature whether the treatment effects of CBTp may be greater for certain subgroups of people with a schizophrenia diagnosis. Such information would prove beneficial for people who have experience of psychosis and for their clinicians when making informed decisions about accessing CBTp. With this in mind, we seek to identify subgroups for which the treatment effect is greatest.

In summary, there an urgent need for evidence based treatments for people with a diagnosis of schizophrenia who are unable to tolerate or have experienced an inadequate response to clozapine. This trial addresses the question of whether CBTp is an effective treatment option for this group.

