### Safety monitoring and reporting

We record all events which meet National Research Ethics Committee (NREC) criteria for a serious adverse event (SAE), i.e. any untoward occurrence that: results in death, is life threatening, results in self-harm, results in harm to others, requires hospitalisation or prolongation hospitalisation, results in persistent or significant disability or incapacity, consists of a congenital anomaly or birth defect, or is otherwise considered medically significant by the investigator. In line with NREC guidance, a SAE occurring to a research participant is reported to the main REC where in the opinion of the Chief Investigator the event is related (i.e. resulted from any of the research procedures) and unexpected. To minimise the risk of bias in the appraisal of whether the event is related and unexpected, we seek an independent opinion for each event from a representative of the IDMC, who is an expert clinician in the area of psychosis. The IDMC and ITSC provide oversight of the adverse events and monitor for any patterns in events between the CBT plus TAU and TAU Alone arms of the trial.

In addition to the above, potential unwanted effects of trial participation will be reported as a PANSS 25 % or more deterioration, scores of six or more on the GCI-Improvement Scale and the adverse effects of trial participation self-report measure.

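### The Discussion and the safety section do not agree on how suicidal crisis without an attempt is counted, so this harm may be incompletely or inconsistently counted between arms

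*Protocol article*

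**What the plan says.** Two places in the protocol article deal with this harm.

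The Discussion presents a published template with four criteria: suicide, suicide attempt, suicidal crisis, and severe symptomatic exacerbation. The third is defined as "explicit plan for serious suicidal activity without suicide attempt as defined by item 8, rating of 2 on the Calgary Depression Rating Scale" for Schizophrenia. The article then says of the first three: "We measure and report criteria 1–3 as part of National Research Ethics Committee requirements for recording and reporting serious adverse events". The next sentence adds that CDSS and CGI scores are also a source of information on unwanted effects. The one after that commits to reporting CGI-Improvement scores of 6 or more at 9 and 21 months.

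The section Safety monitoring and reporting defines an SAE as "any untoward occurrence that: results in death, is life threatening, results in self-harm, results in harm to others, requires hospitalisation or prolongation hospitalisation". It continues with lasting disability and congenital anomaly and closes with an open category: "or is otherwise considered medically significant by the investigator". It then states that "potential unwanted effects of trial participation will be reported as a PANSS 25 % or more deterioration", together with "scores of six or more on the GCI-Improvement Scale and the adverse effects of trial participation self-report measure". The CDSS is not on that list.

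Under Assessment of eligibility and outcome measures, the CDSS is scheduled at baseline, 9 months and 21 months for all participants.

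**The concern.** A reader of the Discussion will take it that suicidal crisis is measured to its stated definition, a fixed rating on a scale item, and reported through the SAE system. The SAE definition printed in the same article contains no reference to that rating, and none of its named categories describes a plan that has not been acted on. The route that would use the rating directly, a count from the CDSS, is missing from the list of unwanted effects to be reported.

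At stake is the comparison of one serious harm between arms. If capture depends on someone hearing of a plan and judging it medically significant, the count depends on opportunity and judgement as well as on how often crises occur. Opportunity differs by design: CBTp participants are offered up to 30 therapy sessions over 9 months in addition to usual care, in a trial where treatment is open. More contact gives more chances for a plan to be disclosed, and a therapist might also apply a different threshold for reporting it. The resulting imbalance could run in either direction, and a similar or different count in the two arms would be hard to interpret.

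**Working it through.** No figure in the article bears on this point, so the check sets the passages side by side.

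**Step 1. Does each template criterion have a route to being counted?**

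- Criterion 1, suicide: a named SAE category (death) covers it.
- Criterion 2, suicide attempt: named categories (self-harm, threat to life, hospitalisation) would normally cover it.
- Criterion 3, suicidal crisis: an attempt is absent by definition, so death and self-harm do not apply. Harm to others, disability and congenital anomaly do not describe it. Hospitalisation applies only where admission follows. Otherwise the remaining route is the investigator's judgement of medical significance.
- Criterion 4, severe exacerbation: CGI-Improvement of 6 or more appears in both sections, and the Discussion gives the time points.

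Criterion 3 is thus the only one of the four with neither a named SAE category that normally fits it nor a stated reporting threshold with time points.

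**Step 2. Is the item 8 rating linked to an SAE record?** No sentence in the article says that a rating of 2 triggers one. The independent opinion sought from a representative of the data monitoring committee concerns whether a recorded event is related and unexpected. It does not decide whether a suicidal plan is recorded in the first place. The safety protocol described under Interventions alerts clinicians to suicidal ideation, but it is not described as counting a harm.

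**Step 3. Do the two lists of unwanted effects agree?** No. The safety section lists PANSS deterioration, CGI-Improvement and the self-report measure. The Discussion adds CDSS scores, but gives them no reporting threshold, time point or table of their own.

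**Step 4. Could the count be made from data already planned?** Yes. The CDSS follows the same schedule in both arms at 9 and 21 months. Assessments fall to research assistants whom the article describes as blinded to allocation. The definition of a case is already printed in the Discussion. A count from item 8 would therefore be standardised and would not depend on how much therapy contact a participant had.

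**Size.** The article gives no rate of suicidal crisis and no expected number of ratings of 2. No under-count can be derived from it, and none is claimed here.

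**The case against.** The strongest case on the other side has four parts.

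First, the two passages can be read as compatible. The open category and the hospitalisation category can both hold a suicidal crisis, and the Discussion says that such events are measured and reported. This stands as far as it goes. A reader might infer that the SAE definition excludes suicidal crisis, so that the harm would come out at or near zero. The text does not support that. It supports only that capture without admission rests on discretion.

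Second, the Discussion names CDSS scores as a source of unwanted effects and gives the item 8 definition shortly before. The ratings will be in the trial data whether or not an SAE form is filed. This also stands, and it is why the events are not lost. It does not settle the matter, because the safety section's own list omits the CDSS and no sentence commits to tabulating item 8.

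Third, there are safeguards: blinded assessors, risk checks at each assessment, and committee oversight of adverse-event patterns by arm. These make a gross failure less likely, but none of them is a rule for counting the event.

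Fourth, this is a journal article, and the ethics-approved protocol and the analysis plan it points to may hold the operational rule. That is a fair limit, and the absence of operational detail is not the point. The point is that two lists which the article does print differ, and that it assigns criterion 3 to a definition that does not name it.

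**Conclusion.** The concern holds in a limited form. The Discussion and the safety section do not match on how suicidal crisis without an attempt is counted. As printed, the SAE route takes it in only through admission or investigator judgement, and the CDSS route is cited in one section and absent from the other. The count may therefore be incomplete, or may differ between arms for reasons other than the true frequency of crises.

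It would go too far to say that the harm will be under-counted, to attach a number to the shortfall, or to say that the article claims full coverage of the template as a strength. The article applies that word to the timing of the primary outcome, 12 months after the end of treatment.

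The conclusion rests on the article alone and assumes that the full protocol does not already link an item 8 rating of 2 to a record or a table. If it does, what remains is to align the article's two sections. The change is worth making because it concerns a serious harm and costs almost nothing.

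**What to change.** Reconcile the two sections as follows.

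- Keep SAE recording as a route for criteria 1 to 3. Removing criterion 3 from it would lose crises that arise between visits and come to light through clinical contact.
- Add to the unwanted effects under Safety monitoring and reporting the number and proportion of participants with CDSS item 8 rated 2, the definition already in the Discussion, at 9 and at 21 months. Report these by arm with a 95% CI, using participants assessed on the item at that visit as the denominator.
- Report suicidal crises recorded as SAEs separately from the CDSS count, since the two sources differ in timing and in how an event comes to be recorded.
- State that visit-based ratings miss crises that resolve between visits.

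The cost is a short addition to the safety section and one further row in the safety table for each visit. The CDSS is already collected on the same schedule in both arms, so no data collection is added and clinical management is unchanged. The article gives March 2017 as the end of data collection, so at the time of writing the rule could still be fixed before the analysis.

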## Abbreviations

ATI, anxious thoughts inventory; AUDIT, alcohol use disorder identification test; BAPS, beliefs about paranoia scale; BCSS, brief core schema scale; CBT, cognitive behavioural therapy; CBTp, cognitive behavioural therapy for psychosis; CDSS, calgary depression rating scale for Schizophrenia; CGI, clinical global impression scale; CGI-P, clinical global impression-participant scale; CHaRT, centre for healthcare randomised trials; CI, confidence intervals; CRN, clinical research network; CTQ, childhood trauma questionnaire; DAST, drug abuse screening test; EPQ, economic patient questionnaire; FOCUS, focusing on clozapine unresponsive symptoms; IDMC, Independent Data Monitoring and Ethics Committee; ISMI, internalised stigma mental illness scale; ITSC, Independent Trial Steering Committee; IVI, interpretation of voices inventory; LN, letter number span; NICE, National Institute for Clinical Excellence; NIHR, National Institute for Health Research; NREC, National Research Ethics Committee; PAM, psychosis attachment measure; PANSS, positive and negative syndrome scale; PROBE, parallel group randomised outcome blinded evaluation; PSP, personal and social performance scale; PSYRATS, the psychotic symptoms rating scale; QPR, process of recovery questionnaire; RA, research assistant; RCT, randomised controlled trial; REC, Research Ethics Committee; SMHRN, Scottish Mental Health Research Network; TAU, treatment as usual; UK, United Kingdom
